### Procedures and randomization

The social support institutions’ that are partners of the study will select potential participants, according to the eligibility criteria of the study and their records of the participants. All eligible older adults will be invited to participate in a singing group program, included in a scientific research study. A briefing will be organized by the research and intervention teams to answer the doubts of the potential participants and to explain the content of the informed consent. After the signing of the informed consent, pre-test measures will be collected, and randomization will be performed. The scientific coordinators of the study will set a numerical ordering of the list of participants and, using the SPSS randomization tool, will split up the participants into two equal groups. The social support institution will assign the selected participants to the intervention program. The participants, singing group facilitators and researchers conducting the study cannot be blinded to allocation. However, the collection of the data, namely, cognitive, psychosocial, motor and physiologic outcome measures will be assessed by independent researchers, blinded to group allocation (see Fig. 3).

**Fig. 3 Fig3:**
[figure not shown]
Timeline of the Schedule of Enrollment, Interventions and Assessments

Data collection will take place for 2 weeks, 10 weekdays, from 10 to 15 participants per day. It will start at 8 am, while participants are fasting, for: I) biomarkers, respiratory function and balance data collection, followed by a buffet breakfast; II) cognitive measurement, followed by a 15 to 20 min break; and IV) psychosocial measurement (questionnaires followed by semi-structured interviews). Every step of data collection will be performed by a different researcher.

### The intervention program

The experimental group will participate in a singing group program that includes several components: (1) relaxation exercises and vocal warm-up; (2) vocal technique component; (3) rehearsal of repertoire component; (4) social component; (5) creation and presentation of a final performance; and (6) assessment of each participant’s performance. Duration: The program is developed over 34 sessions, for 4 months, 2 days a week, 2 h of group singing, with a 20 min break for socialization. Venue: The rehearsals take place in local theatres, outside the day care centers, improving the mobility of the seniors and the contact with the community. A strategy to improve adherence to the intervention program consists in including public figures, well-known singers of this target group, that invited the participants to program, participated in rehearsals and in the final performance (see Table 1).

**Table 1 Tab1:** Singing Group Intervention Program Sing4Health Description (TIDieR: Template for Intervention Description and Replication)

**BRIEF NAME:** Sing4Health - Sing for your Health, Singing Groups Intervention Programme for Older Adults	
**WHY:**	
Previous literature has suggested benefits of singing groups for the well-being, cognitive function and health of older adults. Thus, the objective of this program is to invite a group of older adults to participate in a singing group intervention, to learn a set of exercises and vocal techniques, and collaborate in the creation of a singing show for the general public. The expected benefits of this social and artistic group activity are improvements in the emotional and social well-being, cognitive functioning and general health of the participants.	
**WHAT:**	
**I Materials**:	
One rehearsal room with the capacity for 35 seated individuals and an additional 40 square meters for exercises and activities, one chair for each participant, one piano, one file with lyrics, one bottle of water for each participant, one separate coffee break room, transport for the older adults.	
**II Components and Procedures of the Group Singing Program:**	
**1. Component of physical exercises for relaxation and vocal warm up -** The rehearsals start with 15 mins of relaxation exercises (adapted to the age and physical mobility of the participants) and vocal warm-up exercises. Physical aspects of choral singing are exercised and discussed to promote body awareness, a healthy body posture and understanding of effective breathing during singing. The singing sessions include a combination of sitting and standing up, the use of movements to follow the rhythm and moving to different parts of the room to sing. **Provided by** the intervention team (pianist, maestro) with the support of older adults’ assistants.	
**2. Vocal technique -** The program aims to provide a complete group singing experience for seniors without musical experience, teaching fundamental aspects of singing, sound, voice mechanics and group singing practice. Participants learn correct and healthy vocal production skills, using breathing techniques and listening skills. Participants learn to sing in different parts or voices, which are taught by hearing and repetition. They learn to listen to each other and to synchronize with each other. **Provided by** the intervention team (pianist, maestro) with the support of older adults’ assistants.	
**3. Rehearsal of repertoire –** Sessions involve memorization and interpretation of songs and lyrics using different strategies (learning to listen to separate parts, singing lyrics or musical notation, call and response methods), reviewing previously learned songs and learning to harmonize the individual voices with the rest of the group. The repertoire is proposed by both the intervention team and the participants and selected by the whole group after discussion. The repertoire should also be chosen according to the responsiveness and meaning for the participants and with cultural interest for the community in general. Provided by the intervention team (pianist, maestro, invited artist) with the support of older adults’ assistants.	
**4. Social Component - Break for Socializing and Snacks -** Each session has a break of about 20 min for a snack and socialization among the participants. During the break and at the end of each rehearsal, a social interaction is promoted in which group members share emotions, ideas and expectations about their participation in the program. The sessions also include work oriented towards a common goal, group dynamics exercises and discussions about the meaning of the songs and their cultural history. **Provided by** the intervention team (pianist, maestro) with the support of older adults’ assistants.	
**5. Creation and Presentation of a Public Performance** - The sessions are organized in order to prepare a final performance for the general public. A singer is invited to sing with the group. Families of the participants, older adults from day care centres and the public in general are invited. The participants will benefit from make-up and hair styling before the show. **Provided by** the intervention team (pianist, maestro, and invited artists) make-up artists, supported by the older adults’ assistants.	
**6. Evaluation –** Participants’ tuning will be assessed at the beginning and at the end of the program. To better adjust objectives, the intervention team will monitor the evolution of each participant, in terms of the skills acquired, record of attendance, and achievement of objectives. The quality of the programme and intervention team will be evaluated by the participants by a questionnaire. **Provided by** the intervention team (pianist, maestro), assistant researchers and supported by older adults’ assistants.	
**7. Audio-visual Recoding of the Programme –** A media audio-visual team will collect images from the development of sessions and reports from the participants and the final show, to produce a documentary (20 to 30 min) and two short videos, for the dissemination of the program. The team will be integrated in the singing groups from the beginning. **Provide by** the media team.	
**Team expertise:**	
**Maestro** – Master in Music specialising in Choral Direction by the *Escola Superior de Música de Lisboa*; **Maestro** (Substitute) – Degree in Music in the Community by the *Escola Superior de Educação e Música de Lisboa*; **Pianist** – Master in Jazz Performance by the Royal Welsh College of Music and Drama; **Artistic Director and Invited Artist** – Professional Singer, Musicals’ Performer and Master in Psychology by the Universidade Autónoma de Lisboa; **Invited Artist** – Tenor, Resident Opera Singer of *Teatro Nacional de São Carlos*; **Older Adults’ Assistant** – Degree in Social Education, specialising in Rehabilitation. **Older Adults’ Caretakers** – Professional caretakers from the social support institution. **Training for the Program:** A workshop of two sessions will be provided for all members of the intervention team on the components and goals of the intervention program and on working with the elderly.	
**WHERE**	
Sessions will be conducted in the rehearsal rooms of local theatres in Lisboa and Almada. The performance will take place in public theatres.	
**WHEN and HOW MUCH**	
**Singing Program Duration:** 34 sessions, for about 4 months, 2 days a week, each with 2 h of group singing, with a 20-min break for socializing. **Participants:** Four groups of 30–35 participants.	

While the experimental group is participating in the intervention program, the control group will take part in the usual activities proposed by the day care centers (SCM), and these activities will be registered. After the experimental group finishes the program, the control group will enroll the exact same program. In time three of data collection, the same measures will be collected, representing a follow up for the participants of the first intervention group and a post-test for the second intervention group. All the financial costs of the intervention will be registered and information on all appointments attended in health care services and medication intake by the participants, during the period of implementation of the program, will be collected from both the social care institution and the participants. This will make it possible to calculate the difference between the costs of the program and the expected benefits of the program: for example, if significantly less health care services were used during the intervention periods and its estimated costs (e.g., medical appointments and hospital stays) were therefore lower.

### Ethical procedures

This project follows the international criteria of ethical requirements for studies with vulnerable human participants and for the protection of personal and sensitive data. The research project was approved by an independent Ethics Committee. The terms of participation of the institutions will be subject to written agreement. A debriefing session will be provided by the intervention and researchers team to potentially interested participants, that will sign an informed consent obtained by the social support institution staff, detailing the terms and conditions of participating in the singing program and in the study (available upon request to the authors). Blood samples will be collected, treated and stored for health assessment purposes, following the standards set out in European directives, through the contract of a certified laboratory.

The personal, psychological and health data of the participants will be stored separately, in files password-protected to ensure the confidentiality of the data. During data collection, only the participant number in the survey protocol will be recorded. All information that can identify participants (e.g., name, address, contacts) will be assigned a code number and recorded in a separate file. In a third file, the participant’s number will be associated with the personal information code. The ability to link indirect identifiers with names and addresses remains, but only the coordinator researchers will have access to that link, stored securely and password protected in the study site. If individuals wish to access or modify their registered personal information, they may do so at any time by contacting the scientific coordinators of the study. Data will be archived and kept confidential for at least 10 years after the publication of the results. Data monitoring committee is composed by the research coordinators of the study, independent from the sponsor and of any competing interests. None of the authors of the study have any competing interests. The final trial dataset will not be shared with researchers outside the project team. However, the database will be readily accessible for reviewers in a way that preserves the anonymity of participants.

The order of authorship of the scientific outputs is defined by the scientific contribution in the study, namely, the conception, implementation, writing and scientific supervision, first authored by the PI (Principal Investigator), followed by the co-PI (co-Principal Investigator) and other researchers’ contributors. Important modifications to the protocol will be reported to relevant parties, namely, public protocol registry (NCT03985917) and ethics committee for approval. Research will also follow the standards of scientific integrity and transparency to ensure ethical criteria in the production and dissemination of scientific knowledge.

### Materials

The study aims to measure a set of biopsychosocial variables, described below, divided into four domains: psychoemotional, psychosocial, cognitive and health. All measures will be collected to measure change from baseline at 4 months (post-test) and at 10 months (follow-up).

#### Psychoemotional variables

**Life Satisfaction** will be measured by the Satisfaction with Life Scale (SWLS, Diener, Emmons, Larsen, & Griffin, 1985) validated to the Portuguese by Neto, Barros, and Barros (1990) [48, 49]. Satisfaction with life in general is assessed according to the person’s own criteria. Consists of five items, answered on a 5-point scale from: 1 ‘strongly disagree’; to 5 ‘I agree very much’.

**Positive and Negative Affect** will be measured by the PANAS - Positive and Negative Affect Schedule (Watson, Clark, & Tellegen, 1988) validated for the Portuguese by Galinha and Pais-Ribeiro (2005) [50, 51]. It consists of two scales with 10 items each, which measure the frequency of positive emotions and negative emotions (e. g, “To what extent did you feel each of the following emotions during the last days”: enthusiasm, distress, etc.) on a five points Likert scale (from 1 “nothing or very slightly”; to 5 “extremely”).

**Self-Esteem** will be measured by the Rosenberg Self-Esteem Scale (RSES, Rosenberg, 1965) validated for the Portuguese by Pechorro, Marôco, Poiares, and Vieira (2011) [52, 53]. Assesses the appreciation of self-worth and self-acceptance, with 10 items, answered on a 4-point Likert scale, from 1 ‘strongly disagree’ to 4 ‘strongly agree’.

**Depression, Anxiety and Stress** will be measured by the DASS-21 (Lovibond & Lovibond, 1995) validated for the Portuguese by Pais-Ribeiro, Honrado and Leal (2004), which consists of 21 items distributed over 3 subscales of 7 items each, related to one of the following constructs: depression, anxiety or stress [54, 55]. The response to the items, the extent to which the each sentence applies to the subject in the last 4 months is classified using a Likert 4-point scale ranging, in terms of severity or frequency, from 0 “It did not apply to me” to 3 “Applied to me most of the time”.

#### Psychosocial variables

**Quality of Life** dimensions will be measured by two instruments:
The **World Health Organization Quality of Life – Old** (WHOQOL-OLD) from Power, Quinn, Schmidt, & The WHOQOL-OLD Group, 2005), adapted to the Portuguese by Vilar (2015) [56, 57]. The WHOQOL-OLD measures the quality of life specifically for older adults, with 28 items, measuring six dimensions. In this study the dimensions (1) sensory abilities; (2) autonomy; and (4) social participation will be measured. The items are answered in a 5-point scale, from 1 (Nothing; Very Bad; Very Unsatisfied) to 5 (Extremely; Very Good; Very Satisfied);The **World Health Organization Quality of Life – Bref** (WHOQOL-BREF, WHOQOL Group, 1998) adapted to the Portuguese by Vaz Serra et al. (2006) [58, 59]. The WHOQOL-BREF measures the subjective perception of quality of life. It consists of 26 items, of which two items measure global quality of life and 24 items measure four dimensions. In this study the (1) Physical health, (2) Psychological Health, and (3) Social relationships will be measured. The items are answered in a 5-point scale, from 1 (Very Bad; Very Unsatisfied; Nothing; Never) to 5 (Very Good; Very Satisfied; Extremely; Always).

**Loneliness** will be measured by the UCLA Loneliness Scale (Pocinho, Farate, & Dias, 2010) [60]. Assesses the feeling of being cut off from others, with four items, derived from the longer version of the ULS-20, answered on a 4-point scale from: 0 ‘Never’, to 4 ‘Often / Many Times’.

**Social Identification** will be measured by the Four Item Measure of Social Identification FISI (Doosje, Spears, & Ellemers, 1995) [61]. Assesses the emotional evaluation of the relationship between the self and the ingroup, with four items answered on a Likert scale, ranging from 1 ‘strongly disagree’ to 7 ‘strongly agree’.

**Social Well-Being** will be measured by the Scale of Social Well-Being (Keyes, 1998) adapted for the Portuguese by Silva (2016) [62, 63]. Assesses a multidimensional construct encompassing the dimensions: social acceptance, social coherence, social actualization, social integration and social contribution. In this study we will use a short version of 6 of the 33 items, answered on a Likert scale ranging from 1 ‘strongly disagree’ to 6 ‘strongly agree’.

#### Cognitive function variables

**Cognitive Function** will be measured by the Montreal Cognitive Assessment MoCA (Nasreddine et al., 2005) validated to the Portuguese by Simões et al. (2008) and Freitas et al. (2012) [64–66]. The test measures six cognitive functions: executive function; visuospatial skills; short-term memory; language; attention, concentration and working memory; and temporal and spatial orientation. The maximum score is 30 points, higher scores indicating a better cognitive performance.

**Short-term auditory verbal memory** will be measured by the Rey Auditory Verbal Learning Test (Schmidt, 1996), validated to the Portuguese by Cavaco et al. (2015) [67, 68]. The scale measures the rate of verbal learning, learning strategies, retroactive, and proactive interference, presence of confabulation or confusion in memory processes, retention of information, and differences between learning and retrieval. It consists of a list of 15 unrelated words repeated over five different trials, which participants are asked to repeat in five trials.

**Attention and Executive Function** will be measured by the Trail Making Test (Reitan, 1958) adapted to the Portuguese by Cavaco et al. (2013) [69, 70]. The test measures processing speed, mental flexibility, and divided attention. In this study, TMT A will be used, providing two direct scores: time to complete part A and performance errors.

**Processing Speed** will be measured by the Digit Symbol Test from the Portuguese version of WAIS-III (Wechsler, 2008) [71]. The test measures the processing speed of non-verbal information. It consists of a task of drawing figures corresponding to numbers. It also assesses cognitive and motor speed, planning ability, visual memory, visuomotor coordination, motivation to perform the task and attention.

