Our hypotheses are that participating in group singing will significantly improve the emotional and social well-being, cognitive function, and the general health of the participants after the program, and significantly different to the control group. We also hypothesize that psychoemotional variables (e.g. self-esteem; depression, anxiety and stress), and psychosocial variables (e.g. social identification; loneliness), will mediate the effects of the singing group program on cognitive function (e.g. executive function, verbal memory), well-being and health (e.g. blood biomarkers, respiratory and motor functions) of the participants (see Fig. 1).

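### The Trail Making outcome is labelled executive function, but only Part A (time and errors) is given, which supports a conclusion on attention and processing speed only

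*Protocol article*

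**What the plan says.** The section on cognitive function variables lists four tests: the MoCA, the Rey Auditory Verbal Learning Test (RAVLT), the Trail Making Test and the Digit Symbol Test.

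- **Trail Making.** The outcome label joins attention and executive function. The test as a whole is then described: "The test measures processing speed, mental flexibility, and divided attention". The next sentence is specific to this trial: "In this study, TMT A will be used, providing two direct scores: time to complete part A and performance errors". The Abbreviations list likewise has only TMT-A.
- **MoCA.** "The test measures six cognitive functions: executive function; visuospatial skills; short-term memory; language; attention, concentration and working memory", plus orientation, with a maximum of 30 points.
- **Digit Symbol.** Its label is processing speed. The text adds: "It also assesses cognitive and motor speed, planning ability, visual memory, visuomotor coordination, motivation to perform the task and attention".
- **RAVLT.** "The scale measures the rate of verbal learning, learning strategies, retroactive, and proactive interference, presence of confabulation or confusion in memory processes, retention of information". How learning compares with retrieval is listed as well. The procedure is then given: "It consists of a list of 15 unrelated words repeated over five different trials, which participants are asked to repeat in five trials".

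Executive function comes first among the improvements expected in the section on cognitive functioning aspects. It is also the first example in the mediation hypothesis at the end of the Background, where psychoemotional and psychosocial variables "will mediate the effects of the singing group program on cognitive function (e.g. executive function, verbal memory").

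**The concern.** An outcome label tells the reader what a result may be taken to show. Here the label and the list of functions belong to the Trail Making Test as a whole, while the trial gives one part and takes two scores from it. With the label as it stands, a shorter Part A time in the singing group would naturally be written up as better executive function, and an unchanged time as no executive benefit. Neither conclusion follows from a time and an error count on Part A.

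The article says that the protocol was registered in order to prevent selective outcome reporting. That safeguard works only if each named outcome corresponds to the score collected for it.

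**Working it through.** The plan gives no figure on this point, so there is none to reproduce. The check matches each function that the text attaches to a test with the score or part that the text says is collected.

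**Trail Making: three functions credited, Part A given**

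1. Processing speed: matched by the time to complete Part A.
2. Mental flexibility: no score is identified.
3. Divided attention: no score is identified.

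So 3 − 1 = 2 of the three functions are unsupported, and the executive half of the label has no other basis in this test. The limit to Part A is explicit and trial-specific, and it names the scores. It is therefore not a detail lost in condensing the protocol into an article.

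One assumption comes from general knowledge of the test and is not in the article: Part A is a single-sequence task, and the switching demand lies in the other part. The mismatch does not depend on it, because the article itself credits the whole test and then takes one part. The assumption only explains why attention/processing speed is the label that Part A can carry.

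**Executive function elsewhere in the battery**

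- The MoCA is said to measure executive function as one of six functions. Only the 30-point maximum is stated; no executive score is specified there or in the paragraph on statistical methods.
- Digit Symbol is said to assess planning ability among other things, but it is designated as the processing-speed measure.

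Executive function is therefore covered, but thinly.

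**RAVLT: functions credited, procedure described**

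- Credited, among others: retroactive interference, proactive interference, retention, and learning versus retrieval.
- Described: one list of 15 words over five trials. No interfering list and no delayed recall is mentioned.

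The two statements do not fit each other as written. However, the procedural sentence describes the instrument. It lacks the phrase limiting it to this study that the article uses where it shortens an instrument (the WHOQOL-OLD dimensions, the 6 of 33 social well-being items, Trail Making Part A).

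**The case against.** The strongest reply is that nobody is misled about what is collected: the article describes the whole test, as it does for other instruments, and then says openly that Part A is used and which scores result. It states no rule that Part A will be reported as flexibility. Executive function appears only as an example within the mediation hypothesis, the cognitive aim is phrased in terms of general cognitive function, and neither the sample size nor the power statement rests on this test.

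Much of this stands. It makes the point one of labelling and interpretation, not a fault in the trial's validity. It does not remove the point, because the label itself assigns the Part A result to executive function, and executive function is also a named expected gain.

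Two stronger readings are tempting and are not supported:

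- *A reader might infer that executive function and memory are tested only by Part A and five learning trials.* The same section gives the MoCA, credited with executive function and short-term memory, and Digit Symbol, credited with planning ability.
- *A reader might infer that the RAVLT is given without an interfering list or delayed recall, so that interference and retention cannot be scored.* The article is condensed and does not say that these parts are left out; the full protocol may contain them. Counting them would give six functions without a score. Four of the six depend on this inference, which leaves 6 − 4 = 2, both from Trail Making.

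**Conclusion.** The point holds for the Trail Making Test. Its label and two of its three credited functions go beyond the two Part A scores, so its result supports a conclusion on attention and processing speed, not on executive function. This concerns one of the four cognitive tests and changes no sample size, power or test statistic. What it changes is what the trial may conclude about executive function.

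That a Part A result would be reported as executive function is an expectation drawn from the label, not something the article commits to.

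For the RAVLT, only a minor point remains: the functions listed and the procedure described need to be reconciled. Omission of the other parts is not established.

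**What to change.** In the section on cognitive function variables:

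1. Relabel the TMT-A outcome as attention/processing speed.
2. Remove mental flexibility and divided attention from what the test is said to measure in this trial.
3. State that executive-function conclusions, including those in the expected gains and in the mediation hypothesis, are not drawn from TMT-A. Rest them on the MoCA executive component, name it as such, and acknowledge that it is a limited measure within a 30-point test.
4. As a minor edit, state which RAVLT parts are administered and which scores are taken, and keep only the functions that those scores support. Reducing the outcome to the total over the five trials is not advised, since that could discard scores that are being collected.

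The cost is wording, plus a more modest executive-function claim.

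Adding Part B is not part of this fix. It would be an extra procedure in an already long assessment day. The trial also appears to be under way: it was registered retrospectively, and the statistical paragraph speaks of intervention groups already formed. Outcomes are defined as change from baseline, so a test added now might have no pre-test value for participants already enrolled.
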